### Dynamic neuromuscular stabilization exercises (group 1)

At first, the person learns the correct posture in the sitting and standing position in front of a mirror. They recognize their abdominal muscles and learn how to contract them. Then, the treatment practitioner will teach participants diaphragmatic breathing.

#### Diaphragmatic breathing training

It is recommended to sit in an erect position. The shoulders and neck should be completely relaxing, and the upper abdominal muscles should not be active. The person is asked to push the anterior and lateral walls of the abdomen out during the inhale, and perform eccentric contraction of the abdominal muscles. During exhale, they need to maintain intra-abdominal pressure with abdominal muscle contraction. Exhale time should be longer than the inhale time [29].

During each step and in every situation, diaphragmatic breathing is emphasized so that the patient follows this type of breathing in each prescribed exercise.

The exercises will be performed in four positions: supine, prone, sitting, and standing as follows:

#### Prone position

One turns his head to one side, bending the hand and leg on the same side, then bending the hand and opposite leg.

The shoulders and elbows in 90–90 position, lifting the chest first from the floor and then getting the elbows closer to each other and bearing weight on elbows. Next, they take forearms off the ground and bear the weight on the palms of the hands, and then take the pelvic off the ground to reach the quadruped position. To separate the upper trunk from the lower trunk, move hips to each side while maintaining the upper trunk [33].

#### Supine position

The thigh and knee are positioned 90–90, and the hips are slightly abducted and externally rotated. The person is then asked to raise their hands to grab their knees first and then their toes. To separate the upper trunk from the lower trunk, the patient is asked to rotate the upper trunk to the left and right (without moving the lower trunk) while the arms are straight in front of the chest. Again to separate the upper trunk from the lower trunk, the lower trunk is rotated to the left and right (without moving the upper trunk) by rotating the bent knees to each side.

Simultaneous rotation of the upper trunk to one side and lower trunk to the other is the next step: changing of position from supine to side lying, with upper and lower limb flexion and adduction and trunk flexion and rotation. Then moving from side-lying to prone position while controlling the speed [33].

#### Sitting position

In long sitting position, participants put their hands out of their knees, slowly bend knees and hips, then with a slight external rotation of the hips, they try to grasp the toes. In an erect sitting position on a chair, the soles of feet on the floor, arms hooked, they rotate trunk to each side. In this position, they bend the trunk to each side to lift an object. Then they lift pelvis on each side while the trunk is fixed [34].

#### Sit to stand transformation

They sit erect on the ground, one knee outward and one knee inward (side sitting). Then, with the help of a ladder, they put the foot of the in-warded knee on the ground to bring the knee forward.

In the knee-forward position, they do the forward/backward and lateral weight shifting and trunk rotation to the sides. Then bring the other leg forward and switch to squat position, and then stand upright [28]. During the first to the fifth week, the number of sets and their repetition will be increased based on one’s performance.

### Core stability exercises (group 2)

#### Abdominal muscles contraction

Before starting, participants need to recognize their abdominal muscles and learn how to contract them. They will be asked to maintain abdominal contraction and normal breathing (squeeze abdomen while inhalation and exhalation) in all exercises [24].

#### Supine position

In supine position, participants bend their knees and put soles of both feet on the ground (crook lying). While the spine is in proper position, they pull their navel inward (squeeze abdomen gently) and maintain this condition for 5 s. Then, they do the same exercise with straight knee position. In crook lying position, first participants take the sole of each foot off the ground alternately, then lift both legs simultaneously and take both knees to the abdomen. As they look at the ceiling, they gently take their shoulders off the ground (curl up). Next, while both feet are on the floor, they gently flex and extend their knees (heel slide). Participants do bridging exercises while they contract their abdominal and gluteal muscles [22].

#### Prone position

At first, they do the abdominal contraction in the prone position. Then, they raise their chest so that they are in prone on elbow position. In the same position, they take the pelvis off the ground, while the knees and forearms are on the ground (semi plank). Next, they raise the pelvis to be in the quadruped position [23].

#### Quadruped position

In this position, they contract abdominal muscles, then they do cat-camel exercise. After that, they raise their hands than their legs alternately. In the same position, participants raise the opposite hand and leg simultaneously [24].

#### Side-lying position

While two knees are bent, they push the elbow on the ground to raise their trunk and pelvic off the ground (semi-side bridge) [22].

#### Sitting position

While sitting on a chair and soles of the feet on the floor, they raise their knees to the abdomen alternately [23].

#### Standing position

As they lean against the wall, they contract abdominal muscles and gently lower the trunk as the knees bend [24].

During these 5 weeks, the number of sets and their repetition will be increased based on one’s performance.

### Outcome measures

All primary and secondary outcome measures will be measured by the blind assessor, who is a physiotherapy PhD student and completed a training course of biomechanical assessment tools, at baseline (a day before the first treatment session), the day after the final treatment session (15th session), and at a follow-up measurement after 17 weeks s. A home-based exercise program will be recommended for 17 weeks s’ follow-up based on their exercise group.

#### Primary outcome measure

Primary outcome measure will be balance measured by the Berg Balance Scale.

##### Berg Balance Scale

Berg Balance Scale is a validated tool to measure a patient’s static and dynamic balance. It consists of 14 items (scores from zero to 56) and is a valid and reliable test for PWMS [35]. Berg Balance Scale measures balance in sitting, standing, and most daily activities (such as sitting up, moving from chair to chair, standing with eyes closed).

#### Secondary outcome measures

Secondary outcome measures will be:
Trunk function measured by the Trunk Impairment ScalePostural stability by the Biodex Balance SystemFalling rate by asking the patient or their partner: “During the last 6 months, how many times have you fallen down?”Fear of falling by filling out Activities-specific Balance Confidence questioner.Patient mobility by filling out Multiple Sclerosis Walking Scale-12 questioner and measured by Time Up and Go test.Spasticity scale by filling out Multiple Sclerosis Spasticity Scale-88 questioner and measured by Modified Ashworth Scale.

##### Trunk Impairment Scale

The Trunk Impairment Scale is a tool to assess trunk function ability in static, dynamic, and coordination conditions, with scores ranging from zero to 23. The scores for all items are summed, and a higher score indicates greater trunk function. In all cases, the person is in the sitting position without leaning back and without using their hands. Trunk Impairment Scale has been validated and tested for reliability in PWMS [36].

##### Postural stability

Biodex Balance System SD, 115 VAC (made in the United States) is a balance system consisting of a balance plate with 20° tilt range and various stability from 1 (least stable) to 12 (most stable). It is a valid and objective instrument to assess balance performance [37]. The study subjects will place their bare feet on the plate. Foot angle and location of the heel of each foot are recorded in the first session so that they will not change in subsequent sessions. The screen is adjusted to fit the individual height. Before starting the test, the individual will be familiarized with test’s performance (postural stability and falling risk tests). Participants will be instructed to keep the black circle on the screen in the middle of the screen. The number of repetitions in each test is set to three (20 s each with 10 s to rest interval). The plate stability starts at 12 and decreases by the end of the test based on each person's ability. Overall stability, anterior-posterior and medial-lateral index, and falling risk index for each individual will be recorded.

##### Activities-specific Balance Confidence

Activities-specific Balance Confidence is a questioner that contains 16 items and the participant rates his or her perceived level of balance confidence for each item. Scores range from 0 to 100 (best score). It is validated for PWMS [38].

##### Multiple Sclerosis Walking Scale-12

The Multiple Sclerosis Walking Scale Questionnaire is a subjective questionnaire with 12 items. It is a valid and reliable scale where participants rate the extent to which multiple sclerosis has limited their walking ability during the past 2 weeks (maximum score =100) [39].

##### Time Up and Go test

Time Up and Go test is a valid and reliable test to measure the mobility of PWMS. The tools needed in this test are a chair with proper height, a backrest, and a stopwatch. The person sits on the chair, and 3 m in front of the person is marked. They will be instructed to get up from the chair as quickly as possible, go up to 3 m, turn around and follow the same path and sit on the chair [40]. The assessor records the time spent with a stopwatch. The test is repeated three times, and the average is recorded.

##### Multiple Sclerosis Spasticity Scale-88

Multiple Sclerosis Spasticity Scale-88 measures patient’s pexperience and perception of the impact of spasticity in Multiple Sclerosis with day-to-day symptoms and during functional activities over the previous 2 weeks. It contains 88 questions to quantify spasticity for a total score and in eight clinically relevant and stand-alone subscales: muscle stiffness, pain and discomfort, muscle spasms, activities of daily living, walking, body movements, emotional health, and social functioning [41]. Summation of each item score will be recorded.

##### Modified Ashworth Scale

Modified Ashworth Scale is the most commonly used clinical measure of spasticity. Its validity has been proven in all muscle groups. In this study, the group of knee extensors and ankle plantar flexors will be evaluated. First, the inactive range of motion of the knee and ankle joints is measured by goniometer. To measure the tone of the knee extensors, the individual sleeps in the side-lying position so that hip and knee joints are in extension and head and trunk in a straight line, and the pelvis is supported from behind. The assessor stands behind the patient, with one hand above the knee outside the thigh, which stabilizes the femur. The other hand is above the ankle. Then, for 1 s (with the word one thousand one), the knee is passively moved from maximal extension to maximal flexion. The grade ranges from 0 to 4. To evaluate the tone of ankle plantar flexors, the person lies in the supine position, hip and knee are in extension, head and trunk in the midline. The assessor stands on the test side with one hand on the knee (to keep the lower limb fixed) and the other hand under the foot. He/she then lifts the ankle from maximum plantar flexion to maximal dorsiflexion within one second [42].

### Data analysis

SPSS version 22 will be used for data analysis. We will perform an intention-to-treat analysis for dropout participants during treatment sessions and in follow-up assessment sessions. Conditional mean imputation was performed. Mean (standard deviation) or median (first quartile and third quartile) will be used to describe the quantitative variables according to the distribution of variables, and for categorical variables, frequency (percentages) will be used. Graphical methods, numerical indices, and Shapiro-Wilk’s tests will be used to check the normality of different measures.

To compare quantitative demographic variables between the two groups, an independent *t*-test or nonparametric test, Mann Whitney *U*-test will be used. Chi-squared or Fisher’s tests will be used to compare the categorical demographic variables between the two groups.

A separate regression analysis will be done at each follow-up point (i.e. the day after the completion of the 15th session (T2), and after 17 weeks follow-up (T3) each one including group and baseline (T1) as a covariate. The T2 and T3 follow-up point will be considered primary and secondary, respectively. A non-parametric analysis would be a Mann-Whitney *U*-test of the differences (follow-up minus baseline). A 2-tailed *P* < 0.05 will be considered significant.

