### Sample size calculation

This study, for the first time, compares DNS exercises with CS exercises in PWMS. Due to the lack of previous studies and considering the main goal of study as comparing two groups the day after the completion of the 15th sessions, the Cohen standardized effect size for comparing means of two independent groups was used in this study to calculate the sample size. Considering the probability of the first type error of 5%, the power of 80%, the standard Cohen’s effect size of 0.8, and using G-Power software the sample size was calculated as 26 subjects in each group which increased to 32 subjects to assume the 20% of dropout rate. Another power calculation will be performed at the end of the trial to assure the sufficiency of the sample size.

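### Conditional mean imputation followed by an uncorrected regression gives either an inflated type I error or a diluted treatment effect, depending on an imputation model that the protocol does not state

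*Protocol article*

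**What the plan says.** All quotations are from the protocol article.

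- **Data analysis, population:** "We will perform an intention-to-treat analysis for dropout participants during treatment sessions and in follow-up assessment sessions".
- **Data analysis, missing outcomes:** "Conditional mean imputation was performed". This is the only missing-data method named. The variables on which the mean is conditional are not given, so it is open whether treatment group is one of them.
- **Data analysis, model:** a separate regression at each follow-up, "each one including group and baseline (T1) as a covariate". On timing, "The T2 and T3 follow-up point will be considered primary and secondary, respectively". A Mann-Whitney test on change from baseline is the non-parametric alternative. The threshold is two-tailed, P "< 0.05 will be considered significant".
- **Sample size calculation:** 26 per group, "which increased to 32 subjects to assume the 20% of dropout rate". The calculation is tied to the comparison on the day after the 15th session, which is T2.

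The section mentions no repeated imputation, no added residual noise and no correction to the standard error.

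**The concern.** Conditional mean imputation replaces a missing outcome with its predicted value. That value carries no residual scatter, yet the regression that follows counts it as a measured patient. What goes wrong depends on the predictors.

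- **Group and baseline in the imputation model.** The filled-in points lie exactly on the fitted surface. Adding them leaves the least-squares treatment estimate and the residual sum of squares unchanged. Only the apparent sample size and degrees of freedom grow, so the standard error is too small.
- **Group left out.** Missing patients in both arms receive the same prediction at a given baseline. This pulls the two arms together and dilutes the estimated effect.

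At stake is the primary comparison, the Berg Balance Scale at T2 in a superiority trial of 64 patients. Either its 5% level does not hold, or its effect estimate is biased towards zero.

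**Working it through.** **Inputs from the protocol.** Two-sided alpha 5%, power 80%, standardised effect 0.8, 26 per group raised to n = 32 for 20% dropout, 64 in total, 1:1 allocation, regression on group and baseline.

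**Assumption.** The correlation between baseline and follow-up is not given. The range 0.3 to 0.85 was used, and the result hardly depends on it.

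**Plan's own figure.** The exact two-sample t-test at effect size 0.8 has power 0.791 with 25 per group and 0.807 with 26, so 26 is reproduced. Multiplying by 1.2 gives 31.2, rounded up to 32. With 32 per group, losing 6 leaves m = 26 (18.75% missing); losing exactly 20% leaves m = 25.6.

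**Case A: imputation on group and baseline, T2.** The residual sum of squares is the same with and without the filled-in values. It is divided by 2n − 3 = 61 instead of 2m − 3 = 49, and the design counts n instead of m patients per arm. With baseline roughly balanced:

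naive SE / valid SE ≈ √[((2m − 3)/(2n − 3)) × (m/n)]

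- m = 26: √[(49/61) × (26/32)] = √(0.8033 × 0.8125) = 0.808, so the SE is about 19% too small.
- m = 25.6: √[(48.2/61) × (25.6/32)] = 0.795, so the SE is about 20% too small.

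The naive test rejects beyond t = 2.000 (61 df). On the valid scale with m = 26 that cut-off is 2.000 × 0.808 = 1.615 on 49 df, which has a two-sided tail probability of 0.113. For m = 25.6 it is 0.118.

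| Missing per arm | SE ratio | Type I error (formula) |
|---|---|---|
| 3 of 32 (9%) | 0.904 | 0.076 |
| 6 of 32 (19%) | 0.808 | 0.113 |
| 10 of 32 (31%) | 0.680 | 0.181 |

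Simulation agrees (6,000 trials per setting at about 20% dropout, Monte Carlo SE about 0.003 to 0.004):

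| Setting at about 20% dropout | Type I error |
|---|---|
| 6 of 32 missing, correlations 0.3 to 0.85 | 0.109 to 0.119 |
| Random 20% missing | 0.121 |
| Dropout depending on baseline | 0.133 |
| Mann-Whitney on changes, same imputed data | 0.098 to 0.136 |
| Planned regression on observed data only | 0.048 to 0.054 |

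With 3 of 32 missing per arm (4,000 trials), the simulated figure was 0.074.

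**Case A at T3, with T2 as a further predictor.** Here T2 carries real information on the missing value, so the inflation is smaller: about 0.065 when T2 and T3 correlate at 0.9, rising to about 0.10 at 0.5.

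**Case B: imputation on baseline without group.** A fraction m/n of each arm keeps its treatment contrast and the rest contributes none. The expected effect is 0.80 × 26/32 = 0.65. Simulation gives 0.648 for a true 0.80 and 0.40 for a true 0.50. The type I error is 0.048 to 0.054. The regression's rejection rate under a true 0.80 is 0.977, against 0.978 on observed data. The harm is therefore to the estimate and hardly to the power of the regression.

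**After correction.** With 6 of 32 missing per arm, the planned regression on observed data gives 0.050 to 0.053. Multiple imputation (20 imputations, Rubin's rules with small-sample degrees of freedom) gives 0.043.

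**The case against.** The best defence is that the conditioning variables and any variance correction are details that an article leaves to the full analysis plan. That would excuse silence on missing data. It does not excuse naming a deterministic method and following it with an uncorrected regression. That the imputation is single, and the filled-in values treated as observed, is an inference from this wording, though a natural one.

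Four stronger readings are tempting, and the protocol does not support them.

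- **That the type I error is doubled, without qualification.** This needs group in the imputation model and dropout near 20% at T2. Including group is the natural reading, because it matches the analysis model, but it is not stated. The 20% is a planning allowance. Loss may be lower after a free, home-delivered five-week programme with travel to assessments paid, and at about 6% dropout the error is only about 6%.
- **That every secondary test has standard errors that are too small.** This fails if group is omitted, and the size varies at T3. The regression calculations concern a continuous outcome; fall counts and Ashworth grades were not modelled.
- **That imputation never adds information.** This is true for a model of group and baseline only. It is not true for T3 predicted from T2.
- **That the separate regressions must give way to a mixed model.** They need not: on observed data they hold the 5% level.

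**Conclusion.** The method as written should not stand, because both ways of carrying it out give a wrong result at the planned dropout. With group and baseline in the imputation model, the T2 standard error is about 19 to 20% too small and the type I error is about 11 to 12%. The error is about 7 to 8% at 10% dropout, and about 6.5 to 10% at T3 if T2 is also a predictor. Without group, the 5% level holds but the effect is understated by about 19%.

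These sizes rest on 32 per arm, similar dropout in both arms, dropout at random (or, where stated, dependent on baseline) and an approximately normal outcome. They barely depend on the assumed baseline correlation. Since the protocol does not say which model applies, the direction of the error cannot be settled from the document.

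**What to change.** Delete the conditional-mean sentence and state one of the following for T2 and T3:

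1. The planned regression on group and baseline, using observed outcomes from all randomised patients in their allocated group. This is the smallest change.
2. An equivalent likelihood-based mixed model on all observed T2 and T3 values. It also uses T2 for patients lost before T3.
3. Multiple imputation with group in the imputation model, followed by the planned regression and Rubin's rules.

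A delta-adjusted sensitivity analysis for departures from missing at random is optional. The change costs analysis wording and a little syntax; it needs no additional patients, visits or data. Compared with imputing on group and baseline, standard errors become wider, which is their correct size.

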### Inclusion and exclusion criteria

Patients with a minimum score of 21 from the mini-mental scale examination, ability to walk, having sustained falling during the last 3 months, and at least high school graduation to fill out self-declaration questionnaires will be eligible. Patients with other neurological disorders, multiple sclerosis exacerbation during the last month, apraxia (due to inability to learn and practice the exercises), severe spasticity (score above three based on modified Ashworth scale), having a history of major surgery in the lower extremities, explicit postural abnormalities in the spine and lower limbs such as scoliosis and kyphosis and cardiovascular disease will be excluded.

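### For fall counts, the stated fallback (Mann-Whitney test of change) gives up baseline adjustment and yields no rate ratio; a count model should be named in its place

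*Protocol article*

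**What the plan says.** Under Secondary outcome measures, falling rate is obtained by asking the patient or partner "how many times have you fallen down" over the previous six months. Under Inclusion and exclusion criteria, every participant must qualify as "having sustained falling during the last 3 months".

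The Data analysis section does not separate outcomes. It states that "A separate regression analysis will be done at each follow-up point", with group and the T1 value as covariates; T2 (after session 15) is primary and T3 (17 weeks) secondary. Normality of the measures is checked by graphs, numerical indices and Shapiro-Wilk tests. The non-parametric alternative is a Mann-Whitney "test of the differences (follow-up minus baseline"). The significance rule is "A 2-tailed *P* < 0.05 will be considered significant". The regression family is not named, and the section mentions no count model or rate ratio.

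**The concern.** A number of falls cannot go below zero, and in recent fallers it is likely to have a long right tail. The document shows no counts, so this is an expectation. If the count fails the normality checks, the only alternative on offer is the rank test of change.

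That test has two weaknesses. Subtracting baseline forces a slope of one on the baseline count. When a patient's count varies from period to period the useful slope is smaller, and the subtraction carries baseline noise into the outcome. The test also returns a p-value for a shift in ranks, with no ratio of fall rates, although the outcome is called a rate.

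Falling is secondary, but it is named in the study aim, and the Discussion ties the possible benefit of DNS to fewer falls. With 64 patients there is little power to spare for it.

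**Working it through.** **1. The plan's own figure.** The Sample size calculation section uses an "effect size of 0.8, and using G-Power software the sample size was calculated as 26 subjects in each group", at 5% two-sided error and 80% power. A two-sample t-test by the noncentral t gives 25.52, hence 26 per group. For dropout, 26 × 1.2 = 31.2, hence 32; dividing by 0.8 gives 32.5, hence 33. The stated 26 and 32 therefore reproduce, but they concern a standardised mean difference. No fall rate, dispersion or rate ratio is given, so everything below rests on assumptions.

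**2. What the six-month recall does.** Take six months as 26 weeks, T2 at 5 weeks and T3 at 17 weeks after randomisation (Recruitment procedures). A recalled count at week T covers T weeks after and 26 − T weeks before randomisation. A true rate ratio RR then appears as 1 − (1 − RR) × T/26. For RR = 0.5:
- T2: 1 − 0.5 × 5/26 = 0.904
- T3: 1 − 0.5 × 17/26 = 0.673

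The Discussion places the 17 weeks after the exercise sessions. On that reading T = 22 and the T3 ratio is 1 − 0.5 × 22/26 = 0.577.

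**3. Power of the planned tests under that recall.** Assumed: 32 per group, mean 4 falls in six months, at least one fall at baseline, RR 0.5, gamma-Poisson counts; 250 runs per setting, Monte Carlo error about √(0.25/250) = 0.03.

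| Time | Between / within variance | Raw-count regression | Mann-Whitney of change | Difference |
|---|---|---|---|---|
| T2 | 0.5 / 0.3 | 0.232 | 0.208 | 0.024 |
| T2 | 1.0 / 0.3 | 0.228 | 0.192 | 0.036 |
| T2 | 2.0 / 0.5 | 0.272 | 0.208 | 0.064 |
| T3 | 0.5 / 0.3 | 0.600 | 0.492 | 0.108 |
| T3 | 1.0 / 0.3 | 0.564 | 0.412 | 0.152 |
| T3 | 2.0 / 0.5 | 0.408 | 0.336 | 0.072 |

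**4. A baseline-adjusted count test with a re-randomisation p-value.** Same recall, RR 0.5, a range of assumed rates, 250 runs per setting:
- T2: 0.16–0.49, against 0.14–0.48 for raw-count regression; mostly level with Mann-Whitney.
- T3: 0.38–0.95, against 0.40–0.95 for raw-count regression; about 7–14 points above Mann-Whitney.

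A further set (gamma period noise of shape 2, 200 runs) gave, at T2, count test 0.22–0.31, regression 0.23–0.30 and Mann-Whitney 0.14–0.30. At T3 it gave 0.45–0.53, 0.42–0.48 and 0.23–0.37. Here the T3 gain over regression was 2–11 points, and the gap to Mann-Whitney was wider than in the main set.

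**5. Why not the model-based p-value.** In the settings of step 3, the model-based negative binomial test on the recalled count had power of only 0.01–0.08 at T2. One explanation is that about 21 of the 26 recalled weeks are shared with baseline, so the follow-up count varies less around its prediction than a negative binomial allows. With separate, non-overlapping windows the same test was slightly liberal (type I error 0.05–0.09).

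**6. Type I error of the planned tests.** With separate windows and 400 runs per setting, raw-count regression gave 0.038–0.052 and Mann-Whitney 0.038–0.055. A second set of eight settings (250 runs each) gave 0.03–0.07 for regression. Mann-Whitney gave 0.036–0.072 in seven settings and 0.100 in one. With no treatment effect the two groups are exchangeable, so that one value is best read as simulation error.

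**7. Falls counted since randomisation only.** In the settings of step 3, model-based negative binomial power was 0.42–0.44 at T2 and 0.55–0.72 at T3. These figures are somewhat flattering, because the test is slightly liberal at this size.

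**The case against.** The best defence is that nothing here is invalid. Falling rate is secondary, the Berg Balance comparison is untouched, and a model for a secondary outcome is often left to an analysis plan, which is not shown. The section does not call its regression linear, and no rule says that a failed normality check forces the Mann-Whitney test. Every participant is asked about the same six months, so ignoring observation time is no defect. All of this stands, and it limits the point to the fallback that the article does state.

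A reader might go further and infer that the planned analyses lose up to half the power for falls. The documents do not support that. Losses of that order arise for the Mann-Whitney route when baseline and follow-up falls come from separate windows, where it kept 32–70% of negative binomial power. The protocol's recall windows overlap. Even with separate windows, raw-count regression kept 59–99% and never lost half.

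A reader might also infer that a count model alone repairs the comparison. It does not: at T2, the primary time point, it gains essentially nothing on the recalled count, because most of that count precedes randomisation.

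**Conclusion.** The point holds in a limited form. A skewed fall count would most naturally fall to a Mann-Whitney test of change, which gives up baseline adjustment and provides no rate ratio. Against a baseline-adjusted count analysis this costs roughly 7–14 points of power at T3 and little at T2. Raw-scale regression, if used, loses little or nothing in the main simulations, and both planned tests keep their type I error. The matter is efficiency of the fallback and interpretability, not false positives.

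The size depends on assumed fall rates, dispersion and a rate ratio of 0.5, none of them in the document, and on T3 falling 17 weeks after randomisation. The lack of a rate ratio from the Mann-Whitney route needs none of these assumptions.

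**What to change.** In the Data analysis section, name a separate analysis for falls in place of the Mann-Whitney test of differences: negative binomial regression (log link) on group and log(T1 falls). The log is defined because entry requires a fall within the last three months. Report the DNS/CS ratio with its 95% confidence interval. Take the p-value from re-randomisation within the sixteen blocks of four, since the model-based test is unreliable with 64 patients. A purely model-based interval shares that weakness, so it is better to base the interval on the same re-randomisation.

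State what the ratio means. On the six-month recalled count, exposure is constant, an offset does nothing, and the ratio is diluted by falls before randomisation. A true rate ratio requires counting falls since randomisation, with log weeks of exposure as offset, and hence rewording the fall question under Secondary outcome measures.

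The cost is one paragraph of analysis text and a permutation step outside the model's default output. The second step also changes one question at the two follow-up visits.
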